**Fig. 2 Fig2:**
[figure not shown]
CHAMPION study design flow chart

The study setting includes three National Cancer Institute designated academic medical centers in the mid-Atlantic region of the USA: the University of Virginia (UVa), Johns Hopkins University (JHU), and Virginia Commonwealth University (VCU). The UVa Cancer Center predominantly serves rural areas in South, Southwest, Central, and North-Central Virginia [41] with approximately 11% of the catchment area residents being African American and 4% Hispanic. The Sydney Kimmel Comprehensive Cancer Center at JHU draws patients from Baltimore City and the surrounding area, as well as those seeking clinical trials, with approximately 20% of the patients being African American and 3% Hispanic. The VCU Massey Cancer Center predominantly serves rural areas in Central-East and Central-West Virginia [42, 43], with approximately 27% of the catchment area residents being African American and 6% Hispanic.

Patient inclusion criteria include the following: a diagnosis of stage III/IV prostate cancer, life expectancy of ≥ 6 months, Karnofsky Performance Status [44] ≥ 60, age ≥ 18 years, and the ability to understand English. Exclusion criteria include the following: severe psychiatric problem, prior non-prostate malignancy in the past 3 years (except treated basal cell/squamous cell skin cancer or superficial bladder cancer), and cognitive impairment. A s*evere psychiatric problem* is defined as inpatient psychiatric treatment in the past 6 months, current treatment with antipsychotic medication, current hallucinations, and/or current serious thoughts of suicide. Cognitive impairment is defined as an adjusted error score of > 5 on the Short Portable Mental Status Questionnaire or other issues preventing participation. A decision partner is defined in the eligibility criteria as a person that the patient identifies as supporting the patient in the decision-making. Consistent with the literature definitions [7], the decision partner is most often a spouse, but can also be an adult family member, friend, or spiritual advisor. In the present study, participants were asked to identify a single decision partner. For illustrative purposes, a ‘typical’ patient-decision partner dyad in this study appears as described in Table 1.

**Table 1 Tab1:** A “typical” CHAMPION study dyad (composite case)

	Age	Race	Ethnicity	Insurance	Employment
Patient	67	African American	Non-Hispanic	Public and private	Employed

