### Recruitment

Recruitment began in 2017 at UVa and JHU, and in 2019 at VCU. Participants are screened at each site using a variety of methods, including research team attendance at weekly clinical case discussions, manual chart review, and referrals from the clinical team. In this event-driven design, oncology clinic providers identify relevant events, such as the patient’s need to address starting, changing, or stopping treatment, and then refer eligible patient-decision partner dyads during weekly clinical trials meetings by teleconferences held at all institutions. In addition, the research teams attend weekly case discussions and discuss patients who may meet the eligibility criteria. The research team subsequently reviews these patients’ medical charts to determine eligibility. If a patient is eligible, the research team addresses the opportunity to participate in the study at the patient’s next clinical visit or over the telephone.

After confirming eligibility, the oncologist or another care provider introduces the study to the patient and decision partner. Patients experiencing serologic, radiographic, or symptom progression are contacted by the research team. The majority of patients and/or dyads are approached directly before or after their clinical visit with the medical oncologist. The research team reviews the study and, if the patient and/or the patient-decision partner dyad is willing, engages in an informed consent process to obtain oral consent or a signature from the patient and the decision partner, as approved by the facilities’ institutional review board (IRB). No data is planned to be used for further studies, which would constitute obtaining additional consent from current participants.

A previous version of the protocol required a decision partner for participation, but this requirement was removed after the study began, based on expert advice and research team discussion regarding the additional value of including patients without decision partners in the study. In the decision to include patients without decisional partners, there is a potential limitation in the analyses to compare between those patients who have decisional partners with those without decisional partners. We will plan to examine differences between dyads and single participants, particularly related to decisional conflict, regret, and quality of life.

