### Statistical analysis and power calculation

The main goal of this mixed-methods research is to test whether the decision support intervention is performing as hypothesized and warrants further research; thus, one-sided testing will be employed. The analysis plan assumes accrual (*N* = 158 dyads) for the quantitative portion of the study and a 15% dropout rate and assumes that the research team will have complete data on 134 dyads, providing approximately 89% power to detect an effect size of 0.5 for change in the main outcome measures for the DI group compared to no change in the EUC group using case-wise deletion. These calculations are informed by pilot data. Considering not all participants will be a dyad, and a smaller number will be single participants, it is unlikely that this would affect the power of the study. This will be reported in future dissemination materials once the study is completed.

For quantitative measures, descriptive analyses will be conducted as appropriate. Change in primary outcomes before and after the intervention will be assessed with analysis of covariance models that include the stratification factors (race and decision event), time, intervention arm, and a time-by-intervention-arm interaction. Additional analyses will assess whether the magnitude of change in primary outcome variables is similar between each member of the dyad using regression models that account for the correlation between each dyad and within participants over time. *Intention-to-treat* is defined as the analysis of all eligible patient-decision partner dyads by treatment as randomized, regardless of compliance with the intervention. Depending on the extent to which the data contain missing data, imputation will be considered for both the dyads and individual participants. Two methods will be used: (1) primary results will be based on an intention-to-treat analysis so that all eligible patients who entered the study will be included in the analyses regardless of compliance and (2) analyses will also include analysis of evaluable cases with more than 80% compliance (operationalized as completed all visits, all parts of the intervention but the home module, and had no other protocol violations) [48]. Using intention-to-treat analysis takes into consideration the bias of dropouts, but using both analyses provide more confidence in the conclusions of the trial if both analyses produce similar effects [48].

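### The intention-to-treat population is defined two ways (dyads, then patients) now that single patients are enrolled, and the statements on dropout bias and power go further than the plan supports

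*Protocol article*

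**What the plan says.** All statements are in the Protocol article; unless another section is named, they are in the section Statistical analysis and power calculation.

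- **Population.** Intention-to-treat "is defined as the analysis of all eligible patient-decision partner dyads by treatment as randomized, regardless of compliance with the intervention". Two sentences later the primary results are said to include every eligible patient who entered, whatever their compliance.
- **Single patients.** Under Recruitment, a partner was once compulsory, but "this requirement was removed after the study began". A comparison of dyads with single participants is planned. On power, the article says "it is unlikely that this would affect the power of the study"; no calculation is shown.
- **Power.** "The analysis plan assumes accrual (*N* = 158 dyads) for the quantitative portion of the study and a 15% dropout rate", leaving 134 complete dyads and about 89% power for an effect size of 0.5, "compared to no change in the EUC group using case-wise deletion".
- **Missing data.** Imputation will be considered, depending on how much is missing, for dyads and for individuals. The article adds: "Using intention-to-treat analysis takes into consideration the bias of dropouts".
- **Timing.** Table 3 gives decisional conflict at baseline and 9 months and regret at 9 months. Quality of life and participation preference are listed at 3, 6 and 9 months.
- **Attrition.** Entry requires life expectancy of at least 6 months (Study design, setting, and population), follow-up lasts about 9 months (Recruitment), and a patient who dies is withdrawn (Intervention).

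**The concern.** The primary analysis set should be fixed before anyone sees outcomes. Here one paragraph gives two sets, and since the amendment they differ by exactly the patients who have no partner. An analyst could defend either. The word eligible, used in both, also leaves room to remove someone after randomisation.

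The dropout-bias sentence treats two problems as one. Keeping people in their assigned arm, whether or not they complied, preserves the randomised comparison. It does not supply outcomes that were never measured. For decisional conflict and regret, a patient lost before 9 months has nothing after baseline. Unless a method for those missing values is fixed, the comparison may rest on people who survived and stayed engaged, and that selection can differ between arms when one arm receives a more intensive programme.

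Finally, power is computed on complete dyads, yet the article says that enrolling people who are not dyads is unlikely to matter. That cannot be true of every analysis, because a single patient supplies no partner data.

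**Working it through.** **1. The two populations side by side**

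| Participant | Formal definition (eligible dyads) | Later sentence (eligible patients who entered) |
|---|---|---|
| Patient with a partner | in | in |
| Patient without a partner | out | in |
| Randomised, later judged ineligible | out | out |

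The second row is the contradiction. The third follows from the word eligible.

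**2. The stated power**

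Inputs from the article: 158 dyads, "a 15% dropout rate", effect size 0.5, one-sided test. Not given there, so assumed: alpha 0.05 and equal arms. The article says only that more dyads go to the intervention arm.

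- Complete dyads: 158 × (1 − 0.15) = 134.3, so 134.
- Two-sample t-test with n1 = n2 = 67: non-centrality = 0.5 / √(1/67 + 1/67) = 2.894. On 132 degrees of freedom the one-sided 5% critical value is 1.656, and power = 89.1%.

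The figure reproduces. By the normal approximation, power is 89.4% at 1:1, 89.1% at 1.25:1 and 88.3% at 1.5:1. It is 86.1% at 2:1, which does not match the stated figure.

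**3. Power for analyses that need a partner or a full dyad**

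Let s be the share of participants without a partner (not in the article; a range is tried). Dyads available = 134 × (1 − s), with the same test, alpha and equal arms.

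| s | Complete dyads | Non-centrality | Power |
|---|---|---|---|
| 0 | 134 | 2.894 | 89.1% |
| 10% | 120.6 | 2.745 | 86.1% |
| 20% | 107.2 | 2.588 | 82.3% |
| 30% | 93.8 | 2.421 | 77.6% |

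If single patients are counted in a patient-level analysis, 134 patients remain after 15% loss and power stays at about 89%.

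**4. Who has a post-baseline value after leaving before 9 months**

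| Primary outcome | Post-baseline times | Leaves between months 3 and 9 |
|---|---|---|
| Decisional conflict | 9 months | none |
| Decision regret | 9 months | none |
| Quality of life | 3, 6, 9 months | at least one |
| Participation preference | 3, 6, 9 months | at least one |

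For the first two outcomes, the article's only statements on missing values are case-wise deletion in the power sentence and imputation that may or may not be done. The second planned analysis requires all visits to have been completed. If the intention-to-treat analysis were also run on complete cases, both would depend on reaching 9 months, and their agreement would say nothing about dropout bias.

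**The case against.** The strongest reply is that the dyad wording is left over from before the partner requirement was dropped, and that the surrounding text shows the intent to keep single patients in. The later sentence includes all eligible patients, imputation is mentioned for individuals, and comparing dyads with single participants would be impossible if the latter were excluded. This stands as evidence of intent. It does not remove the conflict, because the formal definition is the one that names dyads.

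Several stronger readings are tempting, and the article does not support them:

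- *Single patients are dropped.* Only the literal definition implies this; other text points the other way.
- *The primary analysis is a completer analysis.* Case-wise deletion appears only in the power sentence, as a planning assumption.
- *Everyone lost before 9 months contributes nothing.* This is true for two of the four primary outcomes. The stated models include time and could use the 3- and 6-month values of the other two.
- *The 89% is wrong.* It follows from its own inputs, already allows for 15% loss, and holds for patients if singles count. Lower figures at 2:1 would mix in an allocation ratio that the article never gives.
- *Deaths alone will use up the 15% allowance.* The article gives no survival figure. With exponential survival and assumed medians of 24, 36 and 48 months, 1 − 0.5^(9/median) gives 23%, 16% and 12% dead by 9 months, which falls on both sides of 15%. The entry criterion of 6 months is a minimum, and stage III patients are eligible.
- *Eligibility will be re-judged after randomisation.* The wording permits it, but eligibility is confirmed before consent and randomisation, and the data analysts are blinded.

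It can also be said that missing-data methods belong in a full analysis plan, which is not shown. That is fair for the detail. It does not cover the article's positive claim that intention-to-treat takes care of dropout bias.

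**Conclusion.** The point holds in a limited form, and the definition is wrong as written. The primary population is stated in two incompatible ways, and the formal one, taken literally, excludes randomised patients without a partner. The dropout-bias statement is unsupported, chiefly for decisional conflict and regret.

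The power reassurance holds for patient-level outcomes if single patients count. It does not carry over to partner or dyad analyses, where power is about 86%, 82% or 78% at 10%, 20% or 30% single. Those figures rest on one-sided 0.05, equal arms and assumed shares of single patients; the article says only that singles are the smaller number. At 10% the loss is about 3 percentage points, so the consequence for power depends on a share that the article does not report.

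**What to change.** 1. Define intention-to-treat as all randomised patients, with or without a partner, analysed in the arm assigned. Use this one definition throughout.
2. Analyse partner and dyad outcomes among those with a partner. Limit the 89% to patient-level outcomes and restate power for partner outcomes from the actual share of single patients.
3. For the outcomes measured at 3, 6 and 9 months, use a likelihood-based repeated-measures model on all available data. For decisional conflict and regret, specify a sensitivity analysis for deaths and dropout.
4. Withdraw the claim that intention-to-treat alone deals with dropout bias.

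Optional: collect the decisional-conflict uncertainty subscale and the regret scale at the existing 3- and 6-month visits. Recruitment began in June 2017, so this would help only participants who have yet to reach those visits.

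The cost of items 1 to 4 is rewording, some analysis work and a less favourable stated power for partner outcomes.

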## Discussion

Despite advances in the available treatment options for patients with advanced prostate cancer, supportive interventions directed towards complex treatment-based decisions made by patients and their decision partners have not been explored in depth. Decision aids have shown promise in oncological disease states [21], but their use has been limited in patients with advanced cancer. Decision partners are a valuable resource to be considered when attempting to assist patients through the process of cancer treatment decision-making. A key strength of the CHAMPION intervention is that decision partners are direct recipients of the intervention. Interventions to engage patients and decision partners represent a novel, sustainable, and scalable way to build on individual and supporter strengths.

The innovative nature of the proposed decision aid is enhanced by mHealth technology and intervention delivery by trained CPN. Low decision aid use, despite well-demonstrated utility, may be a result of dependence on healthcare professional administration. This is likely to be an ongoing barrier, particularly given the increasing demands on provider time and availability. The CHAMPION intervention CPNs are non-healthcare professionals from the patient and decision partner community who receive training to assist patients with various aspects of promoting and maintaining health, as well as in the conduct of research [30, 31, 37]. The National Academy of Medicine [50] (formerly the Institute of Medicine) recommends expanding CPN use and evaluation to improve care access and quality of care, especially among medically underserved and racial/ethnic minority communities.

Minorities with advanced cancer, particularly African Americans, are often faced with ineffective health-related communication in regard to receiving adequate end-of-life care, which may result in overly aggressive, unwanted care [51–53]. Thus, there is a need for a feasible and interactive intervention to improve communication between minorities and healthcare professionals [26, 27]. The CHAMPION intervention incorporates within the balance sheet narratives a multi-faceted approach. This approach utilizes the patient’s decision partner, CPN, and oncology providers for support and decision-making empowerment. This approach also reinforces the important values identified by minority patients and their decision partners, such as spirituality, family, and trusted others [20]. The ability for patient-decision partner dyads to identify and discuss their own priorities using the decision balance sheets—combined with HRQL-PSY graphical summaries and listening to the cancer decision-making audio tutorial—provides a comprehensive decision-making intervention for both the patient and their decision partner. The integration of these values in the mHealth decision aid intervention creates a tailored intervention for each pair, particularly for those from minority groups. The intervention may support minorities in expressing important concerns with their oncology providers, thereby facilitating a clearer treatment decision-making process and improving outcomes.

This novel and feasible intervention approach, incorporating a CPN to administer an mHealth decision aid to patients with advanced prostate cancer and to their decision partners, should assist oncology providers, policymakers, and the public in sustainably improving healthcare system structures to support complex treatment decision-making. CHAMPION procedures and outcomes have the potential to promote better HRQOL, reduce decisional conflict and decision regret in persons affected by advanced prostate cancers in a community and family-centered care context, and, ultimately, to contribute to reducing the disparities in cancer healthcare treatment.

## Trial status

Protocol date and version: August 24, 2018, version 1.11

Date recruitment begin: June 2, 2017

Approximate date of recruitment completion: September 1, 2021

## Data Availability

Upon reasonable request of the corresponding author, qualified investigators will have access to the dataset under a Data Use Agreement.

## Abbreviations

CHAMPION: Cancer Health Aid to Manage Preferences and Improve Outcomes through Navigation
CPN: Community patient navigator
DI: Decision Intervention
EUC: Enhanced usual care
HRQOL-PSY: Psychosocial health-related quality of life
IRB: Institutional Review Board
JHU: Johns Hopkins University
mHealth: Mobile health
QoL: Quality of Life
UVa: University of Virginia
VCU: Virginia Commonwealth University
